**Fig. 1 Fig1:**
[figure not shown]
Study randomization flowchart. The maximally tolerated dose (MTD) is defined as the dose level below the dose producing unacceptable but reversible toxicity and is considered the upper limit of subject tolerance. Unacceptable but reversible toxicities (adverse events) for this study include: second-degree or higher skin burning or blistering, erythema lasting more than 24 hours, severe swelling, pain, ulceration, change in sensation, and/or muscle weakness

### Blinding

This is a single-blind study, and the subjects will be blinded to the procedure (LED-RL phototherapy or mock therapy). The PI and clinical research coordinators (DH and EK) will be aware of the randomization.

### Time frame

This study is designed to conclude in 7 months, which includes subject recruitment, performing procedures with LED-RL phototherapy and mock therapy, and data analysis.

### Statistical analysis

Statistical analysis will be performed using Statistical Package for Social Sciences (SPSS) or similar. Quantitative data will be presented as mean ± standard deviation and range while qualitative data will be presented as number (*n*) and percentage (%). Student’s *t* test will be used to determine if there is a significant difference in the rate of common expected procedural side effects and adverse events between the LED-RL phototherapy group and the mock therapy group. *P* <0.05 will be used as statistically significant. Data analysis relating to protocol nonadherence and any missing data will be consulted with the biostatistics service at UC Davis Clinical and Translational Science Center.

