## Methods/design

### Hypothesis

High-fluence LED-RL phototherapy is safe on human skin.

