### Study design and subject population

This is a single-blind, dose escalation, randomized controlled, phase I study to evaluate the safety of high-fluence LED-RL phototherapy on human skin. The maximum recommended starting dose (MRSD) of 160 J/cm^2^ is based upon previously published maximum doses of LED-RL phototherapy used in clinical studies that demonstrated clinical safety with no adverse events [18, 19]. The study endpoint of 640 J/cm^2^ was chosen due to feasibility, as this dose corresponds to 2 hours of LED-RL phototherapy, and we anticipate decreased subject compliance with LED-RL exposures longer than 2 hours in duration. Additionally in prior studies, the 640 J/cm^2^ dose demonstrated increased anti-fibrotic properties in vitro compared to lower doses of LED-RL [17].

The protocol for dose escalation requires subjects to be enrolled sequentially in groups of five (three subjects randomized to LED-RL phototherapy and two subjects randomized to mock therapy). As this is a single-blind study, subjects will be blinded to the procedure (LED-RL phototherapy or mock therapy).

Subjects in group 1 randomized to LED-RL phototherapy will receive the MSRD of 160 J/cm^2^. The LED-RL dose will be escalated in subsequent groups using the classical method for dose escalation as described by Spilker: starting with dose (X) increased by an equal amount (in this instance: X = 160 J/cm^2^, 2X = 320 J/cm^2^, 3X = 480 J/cm^2^, and 4X = 640 J/cm^2^) [20]. Common expected procedural side effects are mild and are expected to last less than 24 hours, which include warmth, redness (erythema), and swelling (edema). The MTD is defined as the dose level below the dose producing unacceptable but reversible toxicity and is considered to be the upper limit of subject tolerance. Unacceptable but reversible toxicities (adverse events) for this study include: second-degree or higher skin burning or blistering, erythema lasting more than 24 hours, severe swelling, pain, ulceration, change in sensation, and/or muscle weakness. If one or more subject experiences any of these adverse events, then this is the dose one above the MTD, and we will not proceed with this dose or escalate the dose.

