After either an MTD has been established, or the study endpoint of 640 J/cm^2^ has been achieved, an additional 27 LED-RL phototherapy subjects (for a total of 30) and 18 mock therapy subjects (for a total of 20) (determined randomly) will be enrolled to satisfy Hanley’s Rule of Three, such that it can be concluded with 95 % confidence that fewer than 1 person in 10 will experience an adverse event [21]. Of the larger cohort, the study will be stopped if adverse events determined to be device-related equal or exceed 30 %. Each subject will receive a total of nine LED-RL phototherapy or mock therapy procedures, three times per week for three consecutive weeks. The phototherapy regimen of three procedures per week is a standard phototherapy protocol [22]. Each subject will receive a US$50 check for completion of 1 week (total of US$150 for completion of entire study), and subjects will receive a prorated amount in the event of withdrawal from study.

This study has a sample size of up to 65 subjects. Subjects will be recruited from the Sacramento Veterans Affairs (VA) Medical Center. As detailed in the inclusion criteria, subjects may be of any sex, age, and ethnicity. The Standard Protocol Items: Recommendations for Interventional Trials (SPIRIT) checklist, flow diagram, and trial registration data are available as Additional files 1, 2, and 3.

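### Student's t test is named for comparing adverse-event rates, but for yes/no events at 30 v 20 it is undefined at 0 v 0, and the section omits the upper bound that sized the trial

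*Protocol article*

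**What the plan says.** The hypothesis is one sentence: "High-fluence LED-RL phototherapy is safe on human skin". It carries no margin and no acceptable event rate.

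The Statistical analysis section names one inferential method: "Student’s *t* test will be used to determine if there is a significant difference in the rate of" two kinds of outcome, the reactions that the procedure is expected to cause and the adverse events. The arms compared are LED-RL and mock, and the criterion is P "<0.05 will be used as statistically significant". The same section reports qualitative data as counts and percentages.

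Study design and subject population treats adverse events differently. The maximally tolerated dose rule is triggered when one or more subjects has any event on a list. The target for the final cohort is that fewer than 1 person in 10 has an adverse event, with 95% confidence, by the rule of three. Both count people with or without an event. At the final dose the plan enrols "an additional 27 LED-RL phototherapy subjects (for a total of 30) and 18 mock therapy subjects (for a total of 20"). Each escalation group has "three subjects randomized to LED-RL phototherapy and two subjects randomized to mock therapy". The total is given as: "This study has a sample size of up to 65 subjects".

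**The concern.** For adverse events as the design section counts them, the data are 30 zeros and ones against 20 zeros and ones, probably with few ones. A t test fits such data badly in two ways.

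- It divides by a standard error that is zero when nobody in either arm has an event. No event among the 30 LED-RL subjects is the very result on which the sample-size rationale depends.
- Its p-value relies on an approximation that is rough at small counts, so which side of 0.05 it falls on can depend on the test chosen.

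A separate gap lies between the analysis and the aim. A test for a difference, without a margin, cannot establish safety by failing to reject. The statement that could support a limited safety claim is the one-arm upper bound in the design section, and the Statistical analysis section does not carry it forward. Safety is the trial's sole objective and later phase II work is meant to build on it, so the reported analysis should be the one the trial was sized for.

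**Working it through.** **Inputs.** Final-dose arms of 30 and 20, the 10% target and the total of 65 come from Study design and subject population. The test and the 0.05 level come from Statistical analysis; a two-sided test is assumed. The article gives no expected event rates for the comparison, so the rates below are assumptions.

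**The plan's own figure.** Rule of three: 3/30 = 10.0%. Exact one-sided 95% limit with no events: 1 − 0.05^(1/30) = 9.5%. Total: 4 × 5 + 27 + 18 = 65. All reproduce. The bound needs zero events: with 1, 2 or 3 events in 30 the exact limit is 14.9%, 19.5% or 23.9%.

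**Step 1: 0/30 v 0/20.** The difference is 0 and both variances are 0, so t = 0/0 and there is no p-value. Fisher's exact test gives p = 1.00. With a common true rate p, the probability of this table is (1 − p)^50:

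| Assumed common rate | P(0/30 and 0/20) |
|---|---|
| 1% | 0.99^50 = 61% |
| 2% | 0.98^50 = 36% |
| 3% | 0.97^50 = 22% |
| 5% | 0.95^50 = 8% |

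**Step 2: 6/30 v 0/20.** Difference 0.20. Pooled variance = 30 × 0.2 × 0.8 / 48 = 0.10. Standard error = √(0.10 × (1/30 + 1/20)) = 0.0913. t = 2.19 on 48 degrees of freedom, p = 0.033.

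Fisher's test sums the tables with six events in total that are no more likely than the one observed. C(50,6) = 15,890,700 throughout.
- 6 v 0: 593,775 / 15,890,700 = 0.0374
- 1 v 5: 30 × 15,504 / 15,890,700 = 0.0293
- 0 v 6: 38,760 / 15,890,700 = 0.0024

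The sum is p = 0.069. In the other direction, 0/30 v 3/20 gives 0.029 by t and 0.058 by Fisher. Part of this gap is Fisher's own conservatism: Barnard's unconditional exact test gives 0.040 and 0.032 for the same two tables.

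**Step 3: 5/30 v 0/20.** Difference 0.1667. Pooled variance = 30 × (1/6) × (5/6) / 48 = 0.0868. Standard error = √(0.0868 × 0.0833) = 0.0851. t = 1.96, p = 0.056, not significant. The exact one-sided 95% upper limit for LED-RL solves P(X ≤ 5 | 30, p) = 0.05, giving p = 31.9%, about three times the 10% target.

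**Step 4: error rate and power, by full enumeration of the 30 v 20 tables (undefined counted as no rejection).** Type I error of Student's test is 1.8%, 3.2%, 4.3% and 4.5% at common rates of 5%, 10%, 20% and 30%. Power:

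| LED-RL v mock | Student's t | Fisher |
|---|---|---|
| 10% v 0% | 7% | 3% |
| 20% v 5% | 26% | 19% |
| 20% v 0% | 57% | 39% |

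**The case against.** A reader might infer that the safety verdict rests on P>0.05. The documents do not support that. The design section ties its conclusion to the rule-of-three bound, dose decisions follow the listed toxicities, and the larger cohort has its own stopping threshold. The t test is assigned only to a difference between arms, and nothing says that a non-significant result will be read as safe. At 0 v 0 the counts would be reported anyway and the bound would be 9.5%.

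A reader might also blame the t test for low power. Step 4 shows otherwise: power is limited by 30 v 20, and Fisher's test has less in every scenario. Nor are false positives inflated.

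Two readings soften the point and stand in part.

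- The same test covers warmth, redness and swelling, which the article expects to be common, and the mock unit also generates warmth. For those, 0 v 0 is implausible, so Step 1 applies to the listed adverse events only.
- With nine procedures per subject, rate could mean a per-subject count, for which a t test is less odd. The article does not say so, and all-zero counts would still give no p-value.

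Two further matters are secondary. The unequal-variance version gives 0.043 at 4/30 v 0/20 where the pooled version gives 0.092, but Student's strictly means the pooled version. Whether lower doses are pooled (3 × 4 + 27 = 39 v 2 × 4 + 18 = 26) is a detail that an article may leave to the full plan, and pooling gives the same pattern (4 v 0: 0.095 pooled, 0.044 unequal-variance).

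**Conclusion.** The point holds for adverse events counted per subject, and it should be fixed. The named test fits that outcome badly. It has no result at 0/30 v 0/20, a table with probability 61% or 36% if both arms share an assumed rate of 1% or 2%, falling to 8% at 5%. At small counts it can reach significance where Fisher's test does not (6/30 v 0/20). A non-significant difference cannot on its own support the hypothesis, as 5/30 v 0/20 shows. The Statistical analysis section also omits the upper bound that justifies the 30 LED-RL subjects.

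This is no reason to doubt the sample-size arithmetic, which reproduces, or the dose decisions, which do not use the test. The 0 v 0 probabilities depend on assumed low event rates; the figures at given counts depend only on the arm sizes and a two-sided test.

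**What to change.** In the Statistical analysis section:

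1. Name as the main safety analysis the proportion of final-dose LED-RL subjects with at least one adverse event, with an exact one-sided 95% upper limit set against 10%. This carries forward the bound already in the design section.
2. For per-subject event proportions, replace the t test with the risk difference, LED-RL minus mock, and a 95% interval suited to small binary counts, for example Miettinen-Nurminen.
3. Keep one exact p-value, Boschloo or Fisher, chosen in advance and labelled supportive. State that a non-significant value does not demonstrate safety.

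As secondary wording, say which dose groups enter the comparison.

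The cost is wording only; no subject, visit or procedure changes. The downside is power if Fisher's test is chosen (39% v 57% for the t test at 20% v 0%), which is a further reason why the p-value should not carry the safety conclusion.

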## Discussion

To our knowledge, no prior clinical trials have been performed to determine the safety of high-fluence LED-RL phototherapy. This study may provide important safety information on high-fluence LED-RL phototherapy (160 J/cm^2^ up to 640 J/cm^2^) and help facilitate future phase II studies to evaluate the efficacy of high-fluence LED-RL as a potential noninvasive, safe, portable, at-home therapy for treatment of skin fibrosis. In addition, future phase II clinical trials may reference this study to determine an optimal dose of LED-RL phototherapy for treatment of skin fibrosis.

There may be several potential limitations of this study, which may be encountered at the Sacramento VA Medical Center, Mather, CA, USA. There may be bias towards the male sex in a veteran population, with women representing only 9 % of veterans nationwide [24]. Men have more skin collagen and thicker skin in comparison to women [25], and thus may require higher doses of LED-RL to produce an adverse event. Thus, the MTD of LED-RL phototherapy may differ between men and women. In addition, there may be bias in age toward middle-aged and elderly subjects recruited within the veteran population. Since increased age is associated with reduced skin collagen [26], the penetration of LED-RL may be affected, and the total dose that results in an adverse event may vary amongst different age groups. Consequently, the MTD obtained from this study may only be representative for the sampled age groups. Furthermore, there is bias in ethnicity toward Caucasians within the veteran population, with the minority of veterans nationwide being represented by approximately 12 % African Americans, 7 % Hispanics, and 4 % other ethnicities [24]. The research team will attempt to minimize bias by approaching and recruiting subjects of any sex, age, and ethnicity.

To our knowledge, this is the first phase I clinical trial investigating high-fluence LED-RL on human skin. Therefore, we are conducting a single-site clinical trial. This phase I study was designed with consultation from the Clinical and Translational Science Center (CTSC) Biostatistics and Bioethical services. Randomization and recruitment of a variety of subjects will help minimize bias. Limited data exists pertaining to LED-RL safety and effect in different Fitzpatrick skin types or pigmentation. Post-phase I trial statistical analysis will determine differential safety of LED-RL associated with race and ethnicity and examine to see whether this should be further pursued using more subjects with greater power in a future study, or dose stratification based upon pigmentation. Future multicenter phase I studies stratifying race and ethnicity can be done to determine whether different skin types have different MTDs.

Future phase II studies may evaluate the efficacy of high-fluence LED-RL phototherapy as a potential treatment modality for skin fibrosis based upon the safety information obtained from this study. Following successful demonstration of the safety of high-fluence LED-RL phototherapy on human skin, our research group may pursue a phase II split-scar study to evaluate the efficacy of high-fluence LED-RL phototherapy. Successful demonstration of the efficacy of high-fluence LED-RL phototherapy for treatment of skin fibrosis has the potential to benefit many individuals worldwide, as high-fluence LED-RL phototherapy may lack the side effects that are associated with currently available treatment options.

### Study status

This study began enrolling subjects in January 2016 at the Sacramento VA Medical Center, Mather, CA, USA.

## Abbreviations

ASDS, American Society for Dermatologic Surgery; IRB, Institutional Review Board; LED-RL, light-emitting diode-red light; MSRD, maximum recommended starting dose; MTD, maximum tolerated dose; UV, ultraviolet; VA, Veterans Affairs
